## Abstract

**Background:**

Generalized anxiety disorder (GAD) is a prevalent mental disorder characterized by excessive tension, worry, fear, and autonomic symptoms, which brings huge suffering to patients. Insomnia, one of the most common symptoms experienced by individuals with GAD, often exacerbates anxiety symptoms. Electroacupuncture (EA), a non-pharmacological treatment for insomnia, presents several advantages, including significant efficacy, minimal side effects, and high patient acceptance. However, there is a lack of high-quality randomized controlled trials evaluating the efficacy and safety of EA.

**Methods:**

This study was designed as a randomized, sham-controlled clinical trial. 84 eligible patients with GAD-related insomnia will be randomly assigned to receive either three sessions of EA or sham EA weekly for 8 weeks. The primary outcome will be the change in the Pittsburgh Sleep Quality Index (PSQI) score at week 8. Hamilton Anxiety Rating Scale (HAMA), Insomnia Severity Index (ISI), sleep diary entries, actigraphy sleep assessment, 12-item Short-Form Health Survey, and weekly usage of medication will provide a thorough evaluation of sleep, anxiety, and overall living conditions.

**Discussion:**

This study aims to evaluate the efficacy and safety of EA for treating insomnia in patients with GAD, proving EA can enhance patients’ quality of life and reduce their dependence on medications.

**Clinical trial registration:**

ClinicalTrials.gov, identifier ChiCTR2400083326.

## Introduction

1

The essential feature of generalized anxiety disorder (GAD) is excessive anxiety and worry (apprehensive expectation) regarding various events or activities lasting for at least six months (1). The intensity, duration, or frequency of the anxiety and worry is disproportionate to the actual probability or consequences of the anticipated event, significantly disrupting with psychosocial functioning (2). The 12-month prevalence of GAD is 0.9% among adolescents and 2.9% among adults in the general community of the United States (3). In urban China, the prevalence of undiagnosed or diagnosed GAD is 5.3%, with only 0.5% receiving a diagnosis (4). Insomnia is a common clinical condition characterized by difficulty initiating or maintaining sleep (5) and is also a prevalent comorbid symptom in individuals with mental health disorders (6). Many diseases can lead to cognitive deficits and affect mood (7, 8). The etiology of mood disorders and insomnia is multifactorial, with research indicating that distinct personality traits may contribute to a bidirectional interplay with mental disorders (9). Studies have substantiated that sleep disturbances exacerbate negative emotions (10, 11), while mental disorders develop bad habits (12). The survey suggests that individuals suffering from insomnia are fivefold more susceptible to anxiety or depression than those without the condition (13), while approximately half of individuals with GAD report difficulties in initiating sleep, maintaining sleep, or experiencing early morning awakenings (14).

Contemporary medical treatment for GAD-related insomnia primarily encompasses psychotherapy, pharmacotherapy, and physical therapy (15). According to clinical guidelines, evidence supports the benefits of certain types of pharmacotherapy, psychotherapy, or a combination of both for GAD (16). Cognitive Behavioral Therapy (CBT)-guided psychotherapy typically relies on a personalized treatment approach. Several countries have now implemented internet-delivered cognitive behavioral therapy, which has demonstrated efficacy in alleviating mood disorders among patients (17), however, adherence among Chinese patients often falls short of anticipated levels (18). In the context of pharmacological interventions, certain medications demonstrate favorable response and remission rates, as well as good tolerability when used to treat generalized anxiety disorder (GAD), but the effectiveness is not certain due to the relatively few comparative studies (19). Additionally, the variable spectrum of toxicity and side effects of these medications during the initial treatment phase significantly constrain their clinical application (20). Long-term benzodiazepine administration is associated with adverse reactions, increasing the risk of medication tolerance and dependence (21). Consequently, existing therapeutic approaches for generalized anxiety disorder (GAD) accompanied by insomnia frequently fall short of patient expectations.

Acupuncture presents several advantages in treating GAD-related insomnia, including considerable efficacy, convenient operation, minimal side effects, and lack of addictive properties, all of which can enhance patient treatment adherence. In this study, the primary focus was on observing changes in insomnia symptoms before and after acupuncture treatment. Therefore, the main efficacy indicator selected was the Pittsburgh Sleep Quality Index (PSQI). PSQI is used to assess the sleep quality of participants over the past month and is suitable for evaluating the sleep quality of individuals with insomnia and mental disorders (22). Most high-quality clinical studies and reviews related to GAD use the Hamilton Anxiety Scale (HAMA) to assess the level of anxiety in patients (23–25). Consequently, we used the HAMA to comprehensively evaluate both mental and physical symptoms before and after treatment (26). The Insomnia Severity Index (ISI) is a commonly used self-assessment tool for insomnia, evaluating participants’ subjective perception of the nature and symptoms of their sleep disturbances (27, 28). Sleep diaries and actigraphy combine subjective and objective recordings of patients’ sleep parameters (29, 30). The sleep diary provides necessary information for the calculation of actigraphy parameters, while the actometer overcomes recall bias that can occur when patients use sleep diaries. The 12-Item Short-Form Health Survey (SF-12) is a widely used health survey tool for assessing individuals’ health status and quality of life (31). Using the above methods, we conducted a comprehensive evaluation of generalized anxiety disorder related insomnia from both subjective and objective perspectives. Previous studies have suggested that acupuncture and electroacupuncture (EA) are appropriate, safe, and effective alternatives for managing anxiety (32). A clinical trial demonstrated that acupuncture significantly improved Hamilton Anxiety Rating Scale (HAMA) and Generalized Anxiety Disorder-7 (GAD-7) scores in comparison to sham acupuncture, verifying its effectiveness in treating GAD (33). To date, no randomized controlled trial has specifically evaluated the efficacy of electroacupuncture (EA) against sham EA for the treatment of insomnia associated with generalized anxiety disorder (GAD). Consequently, the present study employs a randomized, controlled trial design to identify an effective set of acupoints and to compare its therapeutic effects with those of sham EA.

The effective acupoint combination is derived from the long-term outpatient treatment experience of our research group. Each point works in conjunction with others to collectively reduce anxiety and calm the mind and spirit. The sleep conditions of patients with GAD will be comprehensively evaluated using subjective and objective indicators and scales. This study aims to assess the clinical efficacy and safety of EA in treating GAD-related insomnia, thereby providing substantial clinical evidence for the use of EA in this context.

## Methods

2

### Study design

2.1

This study is a randomized, single-blinded, sham-controlled trial that has been registered with the Chinese Clinical Trial Registry (ChiCTR2400083326. The protocol adheres to the Standard Protocol Items: Recommendations for Intervention Trials (SPIRIT) 2013 (34), as detailed in supplementary file 1. Patients or the public were not involved in the design, conduct, reporting, or dissemination plans of our research. Approval for this study was approved by the Medical Ethics Committee of LongHua Hospital Shanghai University of Traditional Chinese Medicine (NO.2024LCSY020). Any modifications to the protocol will be reported to both the ChiCTR and the Medical Ethics Committee. This protocol is version 1.0. The flowchart of the study is shown in **Figure 1** (Flowchart of the study), while the schedule of enrollment, interventions, and assessment is shown in **Table 1** (Schedule of enrolment, interventions, and assessment).

**Figure 1 f1:**
[figure not shown]
Flowchart of the study. HAMA, Hamilton Anxiety Scale; PSQI, the Pittsburgh Sleep Quality Index; ISI, Insomnia Severity Index; SF-12, 12-Item Short-Form Health Survey.

**Table 1 T1:** Schedule of enrolment, interventions, and assessments.

Study period	Enrolment	Treatment period								Follow-up period	
Time point(Week)	-1~0	1	2	3	4	5	6	7	8	12	20
Sign informed consent	x										
Eligibility screening	x										
Demographic data	x										
Medical history	x										
HAMD	x										
Primary outcomes											
PSQI	x				x				x	x	x
Secondary outcomes											
HAMA	x				x				x	x	x
ISI	x				x				x	x	x
SF-12	x								x		x
Sleep diary entries	x	x	x	x	x	x	x	x	x		
Actigraphy sleep assessment	x								x		
Weekly usage of medication	x	x	x	x	x	x	x	x	x	x	x
Adverse events		x	x	x	x	x	x	x	x		
Success of blinding									x		

### Criteria for diagnosis

2.3

Participants meeting the following criteria will be included

According to the “*Diagnostic and statistical manual of mental disorders: DSM-5” (*
3) released by American Psychiatric Association, the diagnostic criteria for “GAD” are as follows:

Excessive anxiety and worry (apprehensive expectation), occurring more days than not for at least 6 months, about a number of events or activities (such as work or school performance);The individual finds it difficult to control the worry. The anxiety and worry are associated with three (or more) of the following six symptoms (with at least some symptoms having been present for more days than not for the past 6 months): 1) Restlessness or feeling keyed up or on edge. 2) Being easily fatigued. 3) Difficulty concentrating or mind going blank. 4) Irritability. 5) Muscle tension. 6) Sleep disturbance (difficulty falling or staying asleep, or restless, unsatisfying sleep);The anxiety, worry, or physical symptoms cause clinically significant distress or impairment in social, occupational, or other important areas of functioning;The disturbance is not attributable to the physiological effects of a substance (e.g., a drug of abuse, a medication) or another medical condition (e.g., hyperthyroidism);The disturbance is not better explained by another mental disorder (e.g., anxiety or worry about having panic attacks in panic disorder, negative evaluation in social anxiety disorder [social phobia], contamination or other obsessions in obsessive-compulsive disorder, separation from attachment figures in separation anxiety disorder, reminders of traumatic events in posttraumatic stress disorder, gaining weight in anorexia nervosa, physical complaints in somatic symptom disorder, perceived appearance flaws in body dysmorphic disorder, having a serious illness in illness anxiety disorder, or the content of delusional beliefs in schizophrenia or delusional disorder).

### Criteria for exclusion

2.5

Participants will be excluded if they satisfy any of the following exclusion criteria:

Severe heart, liver, kidney, or other major diseases;Anxiety disorders caused by other physical illnesses (e.g., hyperthyroidism, pheochromocytoma, etc.);Other types of anxiety disorders (e.g., social anxiety disorder, obsessive-compulsive disorder, post-traumatic stress disorder), schizophrenia spectrum and other psychotic disorders, or bipolar disorder, etc.;Pregnancy or lactation period;History of drug abuse or addiction;Patients who changed their sedative-hypnotic medication regimen or dose within 2 weeks before the baseline visit or who received other treatments for insomnia (e.g., cognitive behavioral therapy) within 3 months before the baseline visit, which could affect the evaluation of efficacy;With irregular sleep patterns or those engaged in long-term night shifts;Patients who have participated in other clinical medical trials within the last 2 months;With other organic sleep problems, such as sleep apnea syndrome, restless legs syndrome, etc.;Contraindications for acupuncture treatment, such as having other severe life-threatening underlying diseases, or if the selected acupuncture points area has ulcers, abscesses, skin infections, limb deficiencies, etc., making it impossible to perform acupuncture treatment;Patients with a cardiac pacemaker;Patients with metal allergies or fear of EA.

### Criteria for removal

2.6

Patients who did not complete the full course of 24 sessions over 8 weeks and did not provide a primary outcome indicator after treatment.Patients with the above exclusion criteria occurring during treatment;Voluntary patients’ withdrawal from study treatment;Patients who change the regimen/dose of anti-anxiety drugs used in the baseline periodPatients who change the regimen of sedative-hypnotic medication used in the baseline period.

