#### Control group

2.8.2

The acupoints selected for patients in the control group are identical to those used in the treatment group. Patches are affixed to the acupoints (**Figure 3** EA and sham EA manipulation), allowing sham needles to be inserted through the patch and reach the surface of the skin. Because of the flat needle tip, it cannot penetrate the skin (41, 42) (Patent Number: ZL 2023 2 0605629.3). GV20 and GV24^+^ are connected to the same type of electrical stimulator via a special power cord, the internal wires of which have been cut and are not visible externally, lasting for 30 minutes. As a result, the EA device appears to be connected, but no current flows through the wires. In this group, the sham needles (size 0.25*25mm from Guizhou Andi Medical Equipment Co.) and the same electrical stimulator will be utilized.

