### Safety evaluation

2.11

Treatment-related adverse events (AEs) include dizziness, fainting, hematoma, needle breakage, infection, and exacerbation of the condition due to excessive stimulation from acupuncture or EA. Each AE will be documented with details regarding the date of occurrence, severity, relevance, and resolution. Prior to the trial, researchers will undergo a rigorous training program to ensure that they are proficient in both the treatments and the management of AEs. In the event of any observed AEs, the acupuncturist will promptly assess the severity and take appropriate actions. These may include immediate needle removal and cessation of treatment, providing rest, applying gentle pressure to mitigate bleeding and hematoma formation, or referring the patient to a surgeon or other medical professional in cases of needle breakage or infection. Serious AEs will be reported to the safety committee without delay and managed actively. The anxiety level of the participants was evaluated by a trained assessor, who will terminate the trial based on the outcome. Finally, researchers will analyze patient case report form (CRF) data on AEs to evaluate the occurrence of adverse events in this trial, thereby providing valuable insights for the design of future trials.

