### Statistical methods

2.13

Statistical analysis, including a full analysis set based on the intent-to-treat principle and a per-protocol set, will be conducted with SPSS 26.0 software. Continuous variables such as the change in PSQI, HAMA, ISI, SF-12 score compared to the baseline and indicators of sleep diary entries and actigraphy sleep assessment, which is described as mean ± SD or median (interquartile range) will be analyzed by t-test or rank-sum test while categorical variables such as the proportion of patients with reduced medication represented by frequency (composition ratio) will be analyzed by chi-square or Fisher’s exact tests. CIs will be set at 95% with a significance level of 5% (P < 0.05). The success of blinding will be evaluated through Bang’s Index by using the “χ² test” procedure of SPSS 26.0 software. In addition, A subgroup analysis will be conducted based on factors such as age, gender, type of anti-anxiety medication, and type of sedative-hypnotic medication by the “Split File” procedure of SPSS 26.0 software. The confidence interval will be set at 95%, with a significance level of 5% (P < 0.05).

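### Section 2.6 removes randomised patients for post-randomisation events without limiting this to the per-protocol set, which conflicts with the intent-to-treat full analysis set in section 2.13

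*Protocol article*

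**What the plan says.** Section 2.6 of the protocol article has five items:

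1. "Patients who did not complete the full course of 24 sessions over 8 weeks and did not provide a primary outcome indicator after treatment".
2. "Patients with the above exclusion criteria occurring during treatment".
3. "Voluntary patients’ withdrawal from study treatment".
4. A change in the regimen or dose of the baseline anti-anxiety drugs.
5. A change in the baseline sedative-hypnotic regimen.

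Item 2 brings in the whole of section 2.5. That list includes "Patients with metal allergies or fear of EA" and contraindications to needling, for instance "if the selected acupuncture points area has ulcers, abscesses, skin infections".

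Section 2.13 describes the analysis as "including a full analysis set based on the intent-to-treat principle and a per-protocol set". Neither section refers to the other. Section 2.6 does not say whether removal means stopping treatment, stopping follow-up, leaving the full analysis set or leaving only the per-protocol set.

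**The concern.** All five items are met after randomisation. If they decide who enters the main comparison, the arms compared are no longer the arms randomised.

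Two routes to bias are open. One is through the arm: section 2.11 states that "Treatment-related adverse events (AEs) include dizziness, fainting, hematoma, needle breakage, infection", while section 2.8.2 says of the sham needle "Because of the flat needle tip, it cannot penetrate the skin" and that its wires carry no current. Infection caused by needling would therefore fall mainly in the EA arm. The other is through response: patients who do badly may stop treatment or change drugs, and patients who do well may stop a hypnotic.

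The practical risk comes before the analysis. Section 2.6 stands with the eligibility criteria that study staff apply. If staff take removal to mean the end of assessments, the week-8 PSQI is not collected, and no later analysis plan can recover it.

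**Working it through.** **Reading the items against section 2.13**

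- Item 1 has two conditions joined by *and*: an incomplete course and no post-treatment primary outcome. Because it turns on whether the outcome exists, it reads as a rule about data rather than about stopping treatment.
- Item 3 has no such condition. Take a patient who stops after 15 sessions and completes the week-8 PSQI. Item 1 keeps this patient and item 3 removes the same patient. An intent-to-treat set keeps the patient.
- Item 5 concerns sleep medication. Sleep medication is one of the PSQI dimensions listed in 2.9.1, weekly hypnotic use is a secondary outcome in 2.9.2, and 2.13 analyses the proportion of patients with reduced medication. A patient who stops a hypnotic has arguably changed regimen, so 2.6 could remove a patient for reaching that outcome.
- Section 2.8 permits adjustment of the hypnotic dose and temporary zolpidem or eszopiclone. Section 2.6 does not say whether either counts as a regimen change.

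**The plan's own figures (section 2.12)**

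The dropout step reproduces: 33 / (1 − 0.20) = 41.25, rounded up to 42 per arm. The planned difference is 6.24 − 3.69 = 2.55 PSQI points. (With the two stated SDs and 80% power a t-test needs 25 per arm rather than 33. That errs towards a larger trial and does not affect this point.)

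**Illustrative shift from one-sided removal**

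Let a fraction r of one arm be removed, and let those patients' mean change lie g points below the full-arm mean. The mean of those left is then higher by

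shift = r / (1 − r) × g.

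Twenty per cent of 42 is 8.4, taken as 8, so r / (1 − r) = 8/34 = 0.235. With the full margin of 42 − 33 = 9 it is 9/33 = 0.273. The gaps g are assumptions.

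| Removed, one arm only | g (assumed) | Shift | Share of 2.55 |
|---|---|---|---|
| 8 of 42 | 1.5 | 0.35 | 14% |
| 8 of 42 | 3 | 0.71 | 28% |
| 9 of 42 | 1.5 | 0.41 | 16% |
| 9 of 42 | 3 | 0.82 | 32% |

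**Illustrative simulation with removal in both arms**

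Assumptions, none from the documents except the SDs behind the pooled value: no true effect; 42 per arm; SD √((3.63² + 2.45²)/2) = 3.10; propensity to be removed correlated 0.5 with poor response; two-sample t-test; 8,000 trials per row.

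| Removed, EA / sham | Bias (PSQI points) | Type I error |
|---|---|---|
| 20% / 20%, at random | 0.00 | 4.8% |
| 20% / 20%, selective | 0.01 | 5.3% |
| 20% / 10%, selective | 0.24 | 6.8% |
| 10% / 20%, selective | −0.22 | 7.1% |
| 30% / 10%, selective | 0.49 | 10.8% |
| 20% / 0%, selective | 0.50 | 11.5% |

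Selective removal does little harm when it is equal in the two arms. Bias appears when it is unequal, and its sign depends on which arm loses more.

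**The case against.** The strongest reply is that 2.6 never says what patients are removed from. Read as the source of the per-protocol exclusions, it is consistent with 2.13, which names two sets. Set definitions are often left to an analysis plan, and a journal article is a condensed text. This has force. A reader might infer that intent-to-treat is defeated, but that presumes one reading of removal. What remains is that the rule is stated without limit, that item 1 reads as a data rule, and that item 3 overrides it for patients whose outcome is available. This is stated text that conflicts with 2.13, not just detail left out.

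Several stronger readings are not supported:

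- *Assessments stop.* No section says so. Item 3 speaks of study treatment, not follow-up, and Table 1 makes no exception for patients who stop.
- *Patients harmed by EA leave the safety data.* Section 2.11 has every adverse event documented and analysed from the case report forms, and nothing deletes those records.
- *All these removals depend on arm.* This is well supported only for infection from needling, and 2.5 ties skin infection to needling being impossible. Fear of EA could also arise under sham, where patients see the same device and are told they have an equal chance of either group. For withdrawal and drug changes the link is plausible but undocumented. Metal allergy is a weak example, since sham needles also touch the skin.
- *The shift of 14% to 28% estimates the bias.* It places every informative removal in one arm. Losses through harm under EA and through lack of benefit under sham would partly cancel.

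**Conclusion.** The point holds as an unresolved conflict between two stated rules. Section 2.6, followed literally, takes randomised patients out for events that can depend on arm or response, and 2.13 promises an intent-to-treat set that should keep them. Left open, membership of the primary comparison could be decided after data are seen.

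The possible bias cannot be sized from the documents. The range of 0.35 to 0.71 PSQI points rests on 8 removals in one arm, none in the other, and assumed gaps of 1.5 and 3 points. Two-sided removal gives less, and equal removal gives almost none. The documents do not show that the analysis will in fact depart from intent-to-treat. They show that it may, and that the text does not prevent it.

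**What to change.** State in both 2.6 and 2.13 that:

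- the 2.6 items define exclusions from the per-protocol set only;
- every randomised patient stays in the full analysis set, in the arm assigned;
- a patient who meets a 2.6 item is still asked to complete the assessments already scheduled, above all the week-8 PSQI, unless consent to follow-up is withdrawn.

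Section 2.6 should not be retitled as a treatment-discontinuation rule. That would make a drug change look like a reason to stop treatment, which is a clinical matter outside this point. The sponsor should reconcile the sedative-hypnotic item with the dose adjustment and temporary hypnotic use that 2.8 permits, and say which of these count as a regimen change for the per-protocol set.

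The cost is a wording amendment, reported to the registry and ethics committee as section 2.1 requires, and a small effort to follow up patients who stop treatment. No sample size figure changes. Section 2.15 describes recruitment as under way, so the change protects only visits still to come; those already missed cannot be recovered.
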